### Sample size

2.11.

A total of 32 participants per group (*n* = 128) will provide adequate power (β = 0.81, α = 0.05) to assess a mean effect size of 30%, which was calculated based on differences in plasma CRP concentrations and *ex vivo* IL-2 secretion by PHA-stimulated PBMCs between Obese-NG and Obese-T2D participants. The sample size calculation was performed using data from a previous study (43) and the software G*Power. We applied a conservative attrition rate of 30% based on previous controlled feeding studies that ranged from 10–35% (81–85), totaling 166 participants.

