### Study design

2.3.

The NutrIMM study is a prospective, non-randomized, four-arm, parallel-group, unicentre, controlled-feeding trial conducted at the Human Nutrition Research Unit (HNRU), University of Alberta (Edmonton, AB, Canada). A total of one-hundred and twenty-eight participants aged between 18 and 70 years will be assigned with a 1:1 male to female ratio to one of four groups (*n* = 32 per group): Lean-NG, Obese-NG, Obese-GI, Obese-T2D. All participants will be followed up for a total of 4 weeks from the date of group allocation. It will not be possible to blind participants or researchers due to the inclusion specifications of the groups. An overview of the study design is shown in Figure 1.

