## Trial status

As of June 16, 2023, the NutrIMM protocol version is 2.1. Enrollment of participants started in October 2019 and will continue until the desired sample size is achieved. Recruitment is expected to be completed in July 2023.

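### The total of 166 multiplies 128 by 1.30; a 30% attrition rate needs 128/0.70 = 183, so 166 keeps 128 completers only if attrition is at most about 23%

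*Protocol article*

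**What the plan says.** The Sample size section (2.11) attaches the power to 128 participants: "A total of 32 participants per group (*n* = 128) will provide adequate power". Power and alpha appear as "adequate power (β = 0.81, α = 0.05", where the 0.81 is evidently the power, although it is labelled β. The target is given as a percentage: "to assess a mean effect size of 30" per cent, calculated from differences in CRP and ex vivo IL-2 between Obese-NG and Obese-T2D in an earlier study.

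The section then adds an allowance for losses: "We applied a conservative attrition rate of 30% based on previous controlled feeding studies", those studies being ones "that ranged from 10–35% (81–85), totaling 166 participants".

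Two other places bear on the count. Study design (2.3) says "A total of one-hundred and twenty-eight participants aged between 18 and 70 years will be assigned", with 32 per group. Trial status says that enrolment "will continue until the desired sample size is achieved", without saying whether that size counts people assigned, people enrolled or people who finish.

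**The concern.** An attrition rate is a fraction of those who enter. Adding 30% of the required completers to the required completers gives a smaller total than the one from which losing 30% would leave that number. The total of 166 looks like the result of the first operation, while the text describes the second.

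At stake is whether the stated power of 0.81 survives the attrition that the protocol itself plans for. The post-intervention between-group comparison and the paired baseline-to-post tests (Statistical analysis, 2.10) need participants who reach the end. Losses are a realistic prospect, because the Compliance section (2.9.1) excludes participants who cannot keep to at least 90% of the feeding protocol. The count is also unclear between sections: 128 is the number assigned in 2.3, but in 2.11 it is the number before a loss allowance is added.

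**Working it through.** **Inputs (all from 2.11 unless noted)**
- Participants to which the power is attached: 32 per group, 4 groups, N = 128 (also in 2.3)
- Attrition d = 0.30; range in earlier feeding studies 0.10 to 0.35
- Stated total: 166
- Power 0.81, alpha 0.05
- Effect: 30%, with no standard deviation given

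**Step 1. Reproduce the stated total.**
- N x (1 + d) = 128 x 1.30 = 166.4, which rounds to the printed 166.
- N / (1 − d) = 128 / 0.70 = 182.9, so 183.
- Rounding up within groups does not give 166 either: 4 x ceil(32 x 1.30) = 4 x 42 = 168, and 4 x ceil(32 / 0.70) = 4 x 46 = 184.

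Of these four calculations, only multiplication of the total by 1.30 returns 166.

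**Step 2. Size of the gap.** 183 − 166 = 17 participants, or 184 − 166 = 18 with equal groups.

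**Step 3. What 166 protects.** The largest attrition that leaves 128 is 1 − 128/166 = 0.229, about 23%.

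**Step 4. Completers from 166 across the cited range.**

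| Attrition | 166 x (1 − d) | Per group |
|---|---|---|
| 10% | 149.4 | 37.4 |
| 22.9% | 128.0 | 32.0 |
| 30% | 116.2 | 29.1 |
| 35% | 107.9 | 27.0 |

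At the planned 30%, about 116 complete: 128 − 116 = 12 fewer than the number that carries the stated power.

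**Step 5. Effect on power.** The article does not name the test behind the 0.81, so this step needs an assumption. Two readings were tried.

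- *Four-group one-way ANOVA with Cohen's f = 0.30.* Power = P(F′ > F crit), where F′ is noncentral F with 3 and N − 4 degrees of freedom and noncentrality f² x N. For N = 128 the noncentrality is 0.09 x 128 = 11.52 and power is 0.810, which matches the stated 0.81. For N = 116 it is 0.09 x 116 = 10.44 and power is 0.765.
- *Two-group t-test, two-sided, set to power 0.81 at 32 per group.* This implies a standardised difference of d = 0.72. At 29 per group, power is 0.769.

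Both readings put power at roughly 0.76–0.77 with 29 per group, 4 to 5 points below the stated value. Steps 1 to 4 do not depend on either reading.

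The paired tests lose the same participants (29 rather than 32 pairs per group), but the article gives no separate power for them, so no figure can be attached.

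**The case against.** The strongest reply is that the shortfall may never occur. It needs enrolment to stop at 166 and attrition to reach the full 30%. The Trial status sentence can be read as recruiting until 128 have completed, and then there is no loss of power. This stands: the 116 is a conditional figure. It does not rescue 166 as the planning number for 30% attrition.

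A second reply is that completers are not the only people analysed. The between-group comparison is made at each time point, including baseline. Under Withdrawal of participants (2.6), data up to withdrawal may still be used, and those with at least two weeks on the diet are asked about a blood sample before leaving. This also stands. With all 166 at baseline and f = 0.30, ANOVA power would be about 0.91, although the 90% compliance exclusion may remove some people at both time points. The loss therefore falls mainly on post-intervention and paired comparisons.

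Third, f = 0.30 is nowhere stated, and the text describes a difference between two groups. That is correct, so the power figure must carry its assumption. The two-group reading gives nearly the same answer.

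Three stronger readings are tempting and are not supported:
- *That the trial will end with 116 completers.* The article does not fix enrolment at 166 in a way that makes this certain.
- *That only 128 will be enrolled, leaving about 90 (128 x 0.70 = 89.6) after 30% attrition.* Section 2.11 explicitly adds an allowance on top of 128, so the 128 in 2.3 is a wording conflict and not evidence of such a plan.
- *That 30% should not be called conservative because the range reaches 35%.* It lies near the top of 10–35%, and a planner need not take the maximum.

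**Conclusion.** The point holds in a limited form. The 166 is wrong for the premise stated beside it: 30% attrition with 128 retained needs 183 (184 with equal groups), and 166 covers only about 23%. This follows from the article's own figures without further assumptions.

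The consequence for power is modest and conditional. If enrolment stops at 166 and 30% are lost, about 116 complete (29 per group), and power for the post-intervention comparison is roughly 0.76–0.77 instead of 0.81. That range rests on a four-group ANOVA with f = 0.30 or a two-group t-test calibrated to 0.81 at 32 per group.

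Separately, 2.3 (128 assigned) and 2.11 (166 in total) disagree, and Trial status does not say which count ends recruitment. No estimand, analysis method or error rate is affected. The figure still needs correcting, because the trial's stated power rests on it.

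**What to change.** - **Sample size (2.11).** Either state that 166 enrolled keeps 128 completers for attrition up to about 23%, and that at 30% about 116 complete with power of about 0.76–0.77, naming the test and effect size assumed; or give 183 (184 with equal groups) as the number that matches 128 completers at 30%.
- **Study design (2.3).** Reconcile the 128 to be assigned with the 166 in 2.11 by saying whether 128 is the number assigned or the number expected to complete.
- **Trial status.** Say whether the desired sample size counts enrolled participants or completers, preferably per group.

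The cost is wording only, plus a slightly less favourable power statement if 166 is kept. Enrolling more participants is optional. The article expected recruitment to finish in July 2023, so the correction may serve mainly to have the planned size and power reported accurately.

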### Statistical analysis

2.10.

Continuous variables characterizing each study group will be reported as means with standard deviations or medians with interquartile ranges. Categorical variables will be represented as frequencies and proportions. Data will be checked for normality using the Shapiro–Wilk test, and logarithmic transformation will be employed for variables not normally distributed. The main comparisons in this study will be (1) between groups at each time point using analysis of variance with groups as the main effect followed by a multiple-comparison *post hoc* test and (2) within groups using paired *T*-test to assess differences between time points (i.e., baseline vs. post-intervention). Correlation analysis and linear regression models will be performed to verify the associations between outcomes (e.g., immune cell phenotypes and function, and systemic inflammation) and exposure (e.g., dietary intake or metabolic parameters, such as glucose, insulin, HOMA-IR, and HbA1c) variables. Mixed model repeated measures will be used to analyze variables of the OGTT to assess the effects of time, group, and time*group interaction. Overall comparisons of postprandial responses among groups will be determined using the incremental AUC with the trapezoid method. The statistical analyses will be adjusted for potential confounders and their interaction with the main group effect in cases where groups are unbalanced regarding factors such as physical activity level, use of medication (e.g., anti-diabetic drugs), and BMI, sex, and age if groups are not matched as initially planned. Sensitivity analyses will be conducted to verify the effect sizes of the primary outcomes of the study to assess the power and validity of our results. Comparative analyses using pertinent variables (e.g., age, sex, diet, metabolic profile, primary outcomes) will be performed between participants that completed the study with those who did not (i.e., participant dropouts or discontinuers). A *p*-value <0.05 will be considered to be statistically significant. A detailed analysis plan will be developed before the final analysis with a biostatistician.

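### The 30% attrition allowance is computed as 128 × 1.30 = 166 instead of 128 / 0.70 = 183; if enrolment stops at 166 and 30% are lost, about 116 complete and post-diet power falls below the stated 0.81

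*Protocol article*

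**What the plan says.** The Sample size section (2.11) sets the required number: "A total of 32 participants per group (*n* = 128) will provide adequate power (β = 0.81, α = 0.05"). The value labelled β is evidently power, and I treat it so. The target effect is described as follows: "to assess a mean effect size of 30%, which was calculated based on differences in plasma CRP concentrations" and IL-2 secretion, between the Obese-NG and Obese-T2D groups. The calculation was done in G*Power with data from an earlier study.

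The same section then adds the allowance for losses: "We applied a conservative attrition rate of 30% based on previous controlled feeding studies that ranged from 10–35% (81–85), totaling 166 participants".

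The Study design section (2.3) gives the same 128 as the number assigned, 32 per group. The Statistical analysis section (2.10) names two main comparisons: one "between groups at each time point using analysis of variance with groups as the main effect", and a paired comparison of baseline with post-intervention within groups. The Trial status section says that enrolment goes on until the target size is reached, but does not say whether that target is 166 enrolled, 128 completers or something else.

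**The concern.** The step from 128 to 166 adds 30% of the number required. An attrition rate is the proportion of enrolled participants who are lost, and the plan takes its rate from losses seen in earlier feeding studies. The correct step divides by the proportion retained, 1 − 0.30. Multiplying by 1.30 gives too small a total, and the gap widens as the rate rises.

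The enrolment total and the power are figures that the trial relies on. As written they do not agree with each other at the plan's own loss rate. Analyses that need post-diet samples are the ones exposed: the post-intervention comparison between groups and the paired comparison. Losses may come from voluntary withdrawal, from exclusion for less than 90% compliance with the feeding protocol (section 2.9.1), or from acute illness (section 2.13), so the allowance is a working figure.

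**Working it through.** **Inputs.** Required N = 128, four groups of 32; α = 0.05; power 0.81; attrition d = 0.30; stated total 166 (all from section 2.11). Test: one-way analysis of variance on four groups (section 2.10). Assumption: the 30% effect size is Cohen's f = 0.30. The article does not say so.

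**1. Reproduce the plan's total.**
- N × (1 + d) = 128 × 1.30 = 166.4, which matches 166.
- N / (1 − d) = 128 / 0.70 = 182.9, so 183, which does not match.
- Rounding within groups does not rescue 166: 32 / 0.70 = 45.7, so 46 per group and 4 × 46 = 184.

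**2. What 166 delivers.**
- Largest loss that still leaves 128: 1 − 128/166 = 38/166 = 22.9%.
- At the planned 30%: 166 × 0.70 = 116.2, about 116 completers or 29 per group. This is 12 short of 128.
- Shortfall in enrolment against a 30% loss: 183 − 166 = 17.

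**3. Reproduce the plan's power.** One-way analysis of variance, noncentral F, with 3 and N − 4 degrees of freedom and noncentrality f² × N.
- N = 128: noncentrality 0.09 × 128 = 11.52, power 0.810. This matches 0.81, and 128 is the smallest N that reaches 0.81.

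**4. Power of the post-diet comparison if enrolment stops at 166.**

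| Attrition | Completers | Power (f = 0.30) |
|---|---|---|
| 10% | 149.4 | 0.873 |
| 20% | 132.8 | 0.826 |
| 22.9% | 128.0 | 0.810 |
| 30% (planned) | 116.2 | 0.766 |
| 35% (top of cited range) | 107.9 | 0.730 |

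With whole participants, N = 116 gives 0.765. The 35% row shows sensitivity only; the plan does not assume it.

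**5. Check under the other reading of the effect size.** The effect is described through a difference between two groups, so take a two-sided t-test with 32 per group and choose the standardised difference that gives power 0.81. That is d = 0.72. With 29 per group, power is 0.769. The drop is about 4 points, against about 4.5 under the four-group reading.

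**6. Baseline.** If all 166 have baseline data, the same four-group test at f = 0.30 has power of about 0.91, so the error does no harm there.

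**The case against.** The strongest reply is that power need not be lost at all. The Trial status section ties the end of enrolment to reaching the target size, and section 2.3 gives that size as 128. If this means 128 completers, power stays at 0.81 whatever the attrition. This stands as a limit on the consequence, because the article does not settle the stopping rule. It does not rescue the figure: under that rule too, 166 would be the wrong expected enrolment at a 30% loss.

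Second, not every main comparison depends on completers. Groups are also compared at baseline, data collected before withdrawal may still be used, and people who withdraw after at least two weeks on the diet are asked whether they would give a sample (section 2.6). This stands for baseline. An optional early sample is not the four-week measurement.

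Third, f = 0.30 is an inference, and reproducing 0.81 does not prove it. This stands, so the power figures are illustrations. The two-group reading gives a similar drop, and the completer counts do not depend on either reading.

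Two stronger readings are tempting but unsupported:
- A reader might infer that 166 is impossible because four equal groups with equal sexes need a multiple of 8. The allocation "with a 1:1 male to female ratio to one of four groups" is attached to the 128, and 128 / 8 = 16 fits exactly. Dropouts need not fall evenly over groups and sexes, and section 2.5.1 makes matching by age and sex conditional.
- A reader might infer that 30% cannot be called conservative because the cited range reaches 35%. The rate lies in the upper part of 10–35%, whose midpoint is 22.5%, so the word is a matter of judgement.

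**Conclusion.** The arithmetic error is established from section 2.11 alone: 166 follows only from 128 × 1.30, and a 30% loss among those enrolled calls for 183, or 184 with equal groups. As it stands, 166 secures 128 completers up to 22.9% attrition.

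The effect on power is conditional and modest. If enrolment stops at 166 and 30% are lost, power for the post-diet comparison between groups is about 0.76 to 0.77 instead of 0.81. A reader might infer that the stated power will simply not be delivered; the documents do not support that, since enrolment may run to 128 completers or attrition may stay at or below 22.9%. The error changes no test or endpoint. Severity is moderate.

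**What to change.** Correct the sentence in section 2.11 in one of two ways:

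- Keep 166 and state what it provides: 128 completers only if attrition is at most 22.9%, and at 30% about 116 completers (29 per group) with power of about 0.76. Name the effect-size definition used.
- Or state that 183 (184 with 46 per group) is the number that matches a 30% loss.

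In addition, state in the Trial status section whether enrolment ends at 166 enrolled or at 128 completers.

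The cost is a sentence or two. The first option needs no further participants, which matters because recruitment was expected to finish in July 2023; its only price is a slightly less favourable power statement at the planned loss rate.

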### Confidentiality, data management/monitoring and audit

2.12.

Each participant will be assigned a unique study identifier for use on the case report forms, other trial documents, and the study database. All study records and documents will be treated as confidential and held securely in a locked filing cabinet. These will be retained for at least 5 years. The trial manager will make a separate confidential record of the name, date of birth, unique provincial health care number, phone number, email address, and participant screening number, to permit the identification of all participants enrolled in the study, in case additional follow-up is required. Only the trial manager and principal investigator will have access to the master list of the study that contains identifiable information. Study data are primarily managed using REDCap. All data from clinical visits, excluding data from unredacted source documents, will be uploaded to REDCap and securely maintained by the trial manager in electronic form. Medical information is available through the provincial health information system (Connect Care) and can be assessed by the appropriate medical personnel responsible for the participant’s healthcare. All manually entered data will be double-checked by a different member of the research team for accuracy. In addition, further verification of data will occur through the application of range to confirm if entered values are clinically possible values. Computer held data including the trial database will be held securely and password protected. Access to the study information will be limited to the trial staff and investigators. All collected data obtained as a result of this study is considered confidential and disclosure to third parties is only allowed when required by the ethics committee or regulatory authorities. Currently, there is no institutional quality assurance or scheduled audit procedures at the University of Alberta. Monitoring of the data is carried out by the trial manager as the data is collected at the HNRU. The trial manager is responsible to ensure completeness and accuracy of outcomes, adverse events, group allocations, informed consent, and completion/withdrawal. Access to the trial final dataset will be available to study investigators, trial manager, and graduate students. There are no contractual agreements that limit access to data.

### Adverse event reporting

2.13.

For this study, we followed the reporting requirements of the Health Research Ethics Board Biomedical Panel of the University of Alberta. Adverse events and other unintended effects will be collected weekly throughout the study from a self-monitoring form that participants will be asked to fill out daily. In addition to this method, participants will be advised to contact the study team directly to report any events. Expected events of this study, anticipated in the participants regardless of participation in research, may include unknown food allergies, gastrointestinal symptoms, changes in glycemia, and lipid profile. Although physiological changes may occur during participation in the study due to modifications in dietary patterns, they are not considered an adverse event unless they are unfavourable to the participant. To better understand if events could be related to the study we will evaluate the incident, its duration, and severity of symptoms. If a participant reports an incident of suspected foodborne illness we will investigate it to determine if there are other factors that may have caused it (i.e., improper food handling once food taken from HNRU, other illnesses in the household, food intolerance, etc.). Then we would send the food samples kept on site for testing to confirm if there was the presence of pathogens in the food. Only adverse events that are serious and unanticipated will be reported to the Research Ethics Office electronically through the Alberta Research Information Services (ARISE) System. Care will be provided to participants that suffer intervention-related harms. Participants will be instructed to seek medical attention and will be removed from the study if they are unable to comply with the feeding protocol due to acute illnesses not related to the study that may arise. If participants are willing to continue the feeding protocol after an acute illness (e.g., a cold), they will be asked to remain another week in the study to have their final appointments.

### Protocol amendments

2.14.

Protocol amendments, once approved by the research ethics board, were disseminated to investigator team by the research coordinator using direct communications and to trial participants, if pertinent. In addition, updates were posted at ClinicalTrials.gov.

### Dissemination policy

2.15.

The results of this study will be communicated within the scientific community through peer-reviewed publications, presentations at conferences attended by researchers and health professionals, and to the community at large, including coverage of study results in institutional websites and external media. A lay summary will be distributed via email to participants that agreed on communications on their last study appointment. We do not intend to use professional writers and manuscripts will be written by graduate students involved in the project. This trial does not have any publication restrictions. Authorship eligibility will be determined according to the recommendations of the International Committee of Medical Journal Editors guidelines.

